## Abstract

**Background:**

Cancer-related fatigue represents one major cause of reduced quality of life in cancer patients and can seriously affect the physical, emotional, and cognitive functioning impeding coping with the disease. Options for effective treatment of cancer-related fatigue are limited, consisting only of non-pharmacologic interventions like physical activity, psychosocial, and mind-body interventions. Recent evidence suggests that vitamin D_3_ supplementation might alleviate cancer-related fatigue. However, confirmation in a randomized controlled trial is needed.

**Methods:**

In this multicenter, randomized, double-blind, placebo-controlled trial, 456 colorectal cancer (CRC) patients aged 18 years and older are being recruited in three German rehabilitation clinics. Study inclusion requires hospitalization of at least 3 weeks at such a clinic, a diagnosis of non-metastatic CRC (stage I-III), surgical removal of the tumor within the past 9 months, and season-adapted vitamin D insufficiency or deficiency. Eligible patients are randomly assigned to a personalized regimen of vitamin D_3_ or placebo for 12 weeks. In the intervention group, a loading dose of 20,000 or 40,000 IU vitamin D_3_ will be administered daily during the first 11 days, followed by a maintenance dose of 2000 IU daily. Patients will complete questionnaires for secondary outcomes (fatigue subdomains, quality of life and subdomains, depression, functional well-being, and infection frequency). Blood and urine samples will be collected for analyses of safety parameters (hypervitaminosis D, hypercalcemia, hypercalciuria, and renal impairment) and efficacy biomarkers (25-hydroxyvitamin D, HbA_1c_, white blood cell count, leukocyte subtype counts, serum C-reactive protein, uric acid, creatinine, triglycerides, total, low- and high-density lipoprotein cholesterol).

**Discussion:**

This trial tests whether a personalized vitamin D_3_ dosing regimen reduces or prevents fatigue among non-metastatic CRC patients by treating the underlying vitamin D deficiency/insufficiency. If efficacy can be confirmed, personalized vitamin D_3_ supplementation could be used as a tertiary prevention measure in addition to non-pharmacological treatments of cancer-related fatigue in CRC patients. We expect to detect an effect of vitamin D_3_ supplementation on secondary outcomes like quality of life, depression, functional well-being, infections, inflammatory biomarkers, diabetes mellitus, and dyslipidemia.

**Trial registration:**

European Clinical Trials Database: EudraCT-No: 2019–000502-30, January 21, 2019; German Clinical Trials Register (DRKS): DRKS00019907, April 30, 2019.

## Background

Colorectal cancer (CRC, ICD-10 C18–21) accounts for more than 60,000 new cases and more than 25,000 deaths per year in Germany [1]. The prognosis has particularly improved for earlier stages of the disease [2]. However, detriments in the Quality of Life (QoL) often persist [3].

One common cause of reduced QoL in CRC patients is cancer-related fatigue. Multiple observational studies have consistently shown that approximately one-third of CRC survivors suffer from fatigue, not only shortly after diagnosis and initial treatment, but also in the long run [3–5]. Fatigue can be highly distressing for the patients: it negatively affects their physical, emotional, and cognitive functioning, and limits their ability to cope with activities of daily living and work [4–6].

So far, only non-pharmacologic approaches, such as physical activity, psychosocial, and mind-body interventions, were found to be effective in alleviating cancer-associated fatigue [7]. A promising pharmacological approach could be to normalize the vitamin D status in CRC patients with vitamin D deficiency. 25-hydroxyvitamin D (25(OH)D) is the best-established biomarker of vitamin D status and its serum levels are typically very low in CRC patients among all stages [8]. Vitamin D deficiency (25(OH)D levels < 30 nmol/L) was detected among 59% of 2912 CRC patients from a large German study during or shortly after first-line treatment and was strongly associated with poor survival [9]. Results from several observational studies also found associations between low 25(OH)D levels and fatigue, exhaustion, and frailty, both in cancer patients and in the elderly population [10, 11].

To date, few controlled trials have addressed the hypothesis of a beneficial effect of vitamin D_3_ supplementation with respect to fatigue, and they mostly suffered from substantial methodological limitations. A pilot study by Kerley et al. observed reduced fatigue in the vitamin D_3_ group but improvement was not statistically significantly higher than in the placebo group [12]. Of note, the trial included only 19 patients with obstructive sleep apnea [12]. A trial by Khan et al. among 60 women with breast cancer observed no statistically significant effect of vitamin D_3_ supplementation on change in fatigue scores over 5 weeks (*p* = 0.15) but was limited by lack of randomization and adequate statistical power [13].

Recently, two randomized placebo-controlled vitamin D trials in general population samples with the endpoint fatigue were published. The trial by Nowak et al. included 120 subjects with hypovitaminosis D (25(OH)D levels < 50 nmol/L) and fatigue who were randomized to either one-time 100,000 IU vitamin D_3_ or placebo [14]. A statistically significant (*p* = 0.01) reduction of the fatigue score was observed 4 weeks after the intervention, which correlated with the rise in the serum 25(OH)D levels. In a smaller trial by Witham et al., 50 individuals were randomized to 100,000 IU vitamin D_3_ or placebo every 2 months for 6 months but no effect was found [15]. However, the trial did not exclude subjects with normal 25(OH)D levels (> 50 nmol/L) and the mean baseline 25(OH)D level was 46 nmol/L. Since supplementation appears to be most beneficial to people with vitamin D deficiency [16], it may not be surprising that supplementation did not show a statistically significant effect in this small, apparently healthy trial population.

The randomized, placebo-controlled, double-blind VICTORIA trial will test the efficacy of vitamin D_3_ supplementation over 12 weeks on fatigue in non-metastatic CRC patients with low vitamin D status. The proposed trial will be by far the largest to address the efficacy of vitamin D_3_ supplementation on fatigue as a primary outcome and the first to be conducted in non-metastatic CRC patients in whom the prevalence of vitamin D insufficiency/deficiency and fatigue are particularly high. It will employ a novel approach using a personalized vitamin D_3_ loading dose and will have adequate power to detect a clinically relevant reduction in fatigue.

### **Objectives**

The primary objective of this trial is to test whether a personalized vitamin D_3_ dosing regimen reduces or prevents fatigue (primary outcome) among stage I-III CRC patients with season-adapted vitamin D insufficiency or deficiency.

The secondary objectives are to assess the efficacy of the treatment on sub-domains of fatigue (physical, emotional and cognitive), QoL (overall and domain-specific), probable depression, functional well-being (FWB), infection frequencies, and various biomarkers (25(OH)D, HbA_1c_, white blood cell count, leukocyte subtype counts, serum c-reactive protein (CRP), uric acid, creatinine, triglycerides, total, low-density lipoprotein (LDL) and high-density lipoprotein (HDL) cholesterol). The study further aims to evaluate the safety of the treatment regarding the occurrence of hypervitaminosis D, hypercalcemia, hypercalciuria, and renal dysfunction.

## Methods/Design

### **Study design**

The trial is conducted as a national multicenter, randomized, double-blind, and placebo-controlled phase III trial using a confirmatory approach. By applying a parallel group design, the participants are randomly assigned in a 1:1 ratio to either the intervention group or to the control group. Recruitment is carried out in three large German rehabilitation clinics and is assumed to take approximately 24 months. The list of trial sites can be obtained from the German Clinical Trials Register (DRKS00019907).

The trial protocol and this manuscript have been developed in line with the Standard Protocol Items: Recommendations for Interventional Trials (SPIRIT) guideline [17].

### **Outcomes and endpoints**

The trial outcomes have been chosen in order to determine the efficacy and the safety of the intervention.

The primary outcome **fatigue** will be evaluated by using the **Functional Assessment of Chronic Illness Therapy-Fatigue (FACIT-F) fatigue subscale**, version 4.0, a commonly used and well-validated measure of fatigue in people with cancer and other chronic health conditions [18]. The tool assesses self-reported tiredness, weakness, and difficulty conducting common activities due to fatigue. Higher scores represent less fatigue. The primary endpoint will be measured as the mean difference in FACIT-F fatigue subscale between intervention and placebo group at trial week 13–16. A mean difference of ≥3 FACIT-F fatigue subscale points will be considered a clinically relevant difference [19]. Additionally, the mean difference in change of FACIT-F fatigue subscale from baseline to trial week 13–16 between intervention and placebo group will be determined as a secondary endpoint.

**Subdomains of fatigue** will be evaluated using the **European Organization for Research and Treatment of Cancer – Cancer related Fatigue (EORTC QLQ-FA12) questionnaire.** This is an alternative to the FACIT-F fatigue subscale without being a global fatigue assessment tool [20, 21], with higher scores representing more severe fatigue. Items which are relevant for the VICTORIA study include physical, emotional and cognitive fatigue domains. They will be assessed as the mean differences in EORTC QLQ-FA12 physical, emotional and cognitive fatigue scores between intervention and placebo group at trial week 13–16 as well as mean differences in changes in these scores from baseline to trial week 13–16 between intervention and placebo group.

**Quality of life** will be determined with the **European Organization for Research and Treatment of Cancer – Core Quality of life questionnaire with 30 items (EORTC-QLQ-C30),** version 3.0. The questionnaire is used to gauge the overall and domain-specific QoL in cancer patients [22]. Higher scores represent better functioning. Items which are relevant for the VICTORIA study include the five functional scales (assessing physical, role, emotional, cognitive, and social functioning) and one global health status/QoL scale. Endpoints are the mean differences in overall and domain specific quality of life scores of the EORTC QLQ-C30 questionnaire between intervention and placebo group at trial week 13–16 as well as mean differences in changes in these scores from baseline to trial week 13–16 between intervention and placebo group. Mean differences ≥5 points in the overall and domain specific scores of the EORTC QLQ-C30 will be considered clinically relevant differences [23].

**Probable depression** will be ascertained with the **Geriatric depression scale (GDS-15)** which has been developed for use among older adults [24, 25]. The focus on the elderly is crucial for this trial as the mean age of the CRC patients to be included is expected to be approximately 65 years. An overall score ≥ 5 points is considered as probable depression [25]. Endpoint will be the mean difference in GDS-15 scale between intervention and placebo group at trial week 13–16 as well as the mean difference in changes in this scale from baseline to trial week 13–16 between intervention and placebo group.

The **FACIT-F FWB subscale** will be used to assess the **FWB** by querying about limitations in the ability to work, coping with the disease, and general life satisfaction [18]. Higher scores represent better well-being. Endpoint will be the mean difference in the FACIT-F FWB score between intervention and placebo group at trial week 13–16 as well as the mean difference in changes in this score from baseline to trial week 13–16 between intervention and placebo group.

**Infection frequency** will be assessed by a self-developed questionnaire. Participants will be asked to state the number of infection episodes for the following infections during the last 12 weeks: Infections of the upper and lower respiratory tract, gastrointestinal infection with diarrhea, cystitis, and fever higher than 38 °C. The total infection frequency will be the sum of all reported infection episodes. If this sum is lower than the number of stated fever episodes with ≥38 °C, the latter will be used as the total infection frequency. Endpoints will be the mean differences in infection frequencies (total, upper respiratory, and lower respiratory tract infections) between intervention and placebo group at trial week 13–16.

Finally, serum und urine parameters will be measured at every sample collection to evaluate the following secondary endpoints:
Mean difference in levels of total serum 25(OH)D between intervention and placebo group at trial day 12–21 and in trial week 13–16 as well as mean difference in change of levels of total serum 25(OH)D from baseline to trial day 12–21 and from baseline to trial week 13–16.Mean serum 25(OH)D levels > 50 nmol/L in intervention group at trial day 12–21 and in trial week 13–16.Mean differences in levels of biomarkers (white blood cell count (WBC), leukocyte subtype counts (band neutrophils, segmented neutrophils, eosinophils, basophils, lymphocytes, and monocytes), serum CRP, serum uric acid, serum creatinine, serum total cholesterol, serum LDL cholesterol, serum HDL cholesterol, and serum triglycerides between intervention and placebo group at trial day 12–21 and in trial week 13–16 as well as mean difference in change of levels of these biomarkers from baseline to trial day 12–21 and from baseline to trial week 13–16.Mean difference in HbA_1c_ levels between intervention and placebo group at trial week 13–16 as well as mean difference in change of HbA_1c_ levels from baseline to trial week 13–16.Differences in frequency of safety parameters (including hypervitaminosis D, hypercalcemia, hypercalciuria, and renal dysfunction (estimated glomerular filtration rate (eGFR) < 30 ml/min/1.73 m^2^) between intervention and placebo group at trial day 12–21 and in trial week 13–16.Mean differences in levels of safety parameters (including albumin-corrected serum calcium, urine calcium/creatinine ratio, and eGFR) between intervention and placebo group at trial day 12–21 and in trial week 13–16.

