### **Statistical analysis plan**

#### Sample size estimation

The sample size calculation is based on the primary endpoint FACIT-F fatigue subscale. We assume that the FACIT-F fatigue subscale is approximately normally distributed. An increase in the FACIT-F fatigue subscale by three points was found to be a clinically relevant reduction of fatigue [19]. The assumed mean and standard deviation of the FACIT-F fatigue subscale are taken from the representative study of Jones et al. [4], which were 38.5 and 10.8, respectively. With a significance level of 0.05 and 80% power, 205 patients are needed in each group to detect a score difference of three or more points using a two-sample t-test for the mean difference, i.e. 410 patients are required in total. The number of patients to be randomized was calculated assuming a 10% drop-out rate. With these assumptions 500 CRC patients need to be screened and 456 eligible persons randomized to achieve the analyzable sample size of *n* = 410.

Given the annual number of overall 1400 eligible CRC patients reported by the participating three rehabilitation clinics in 2016, recruiting of 456 eligible stage I-III CRC patients should be feasible within 24 months.

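### The definition of total infection frequency contradicts itself: read literally, fever is part of the sum, and the fever fallback can then never apply

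*Protocol article*

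**What the plan says.** The rule stands in the infection frequency paragraph of the protocol article, section Outcomes and endpoints. The instrument is a questionnaire that the investigators developed themselves. The paragraph proceeds in four steps.

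- The question: "Participants will be asked to state the number of infection episodes for the following infections during the last 12 weeks".
- The items: "Infections of the upper and lower respiratory tract, gastrointestinal infection with diarrhea, cystitis, and fever higher than 38 °C". Fever is the fifth item in the list.
- The total: "The total infection frequency will be the sum of all reported infection episodes".
- The fallback: "If this sum is lower than the number of stated fever episodes with ≥38 °C, the latter will be used as the total infection frequency".

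The endpoints follow: "Endpoints will be the mean differences in infection frequencies (total, upper respiratory, and lower respiratory tract infections"), compared between the arms at trial week 13–16. Infection frequency is also among the secondary objectives in the Objectives section.

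**The concern.** The list introduces fever as one of the infections to be counted, and the total takes in every reported episode. Fever is usually a sign of one of the other listed infections and not a further infection. A programmer who follows these two sentences would add it to the infection that caused it. The total would then mix the number of infections with how often they were febrile. The fallback would never fire, and it would raise no error to reveal the problem.

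A programmer who starts from the fallback would instead keep fever outside the sum and obtain a different total from the same answers. What is at stake is whether one named secondary endpoint has a single value per participant. If the choice stays open until the data are seen, two totals are available.

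A smaller inconsistency sits in the same paragraph: fever is described once as above 38 °C and once as 38 °C or more.

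**Working it through.** The article states no figure for this endpoint, so there is none to reproduce. The check is one of logic.

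**Inputs.** All come from the infection frequency paragraph. Let U, L, G, C and F be the reported episodes of upper respiratory infection, lower respiratory infection, gastrointestinal infection, cystitis and fever, each a non-negative whole number. Let N = U + L + G + C.

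**Reading A, fever in the sum (list and sum sentence taken literally).** The sum is N + F. The fallback needs N + F < F, that is N < 0, which is impossible. The total is always N + F.

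**Reading B, fever outside the sum (as the fallback presupposes).** The sum is N. The fallback needs N < F, which can occur. The total is max(N, F).

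**Enumeration.** Letting each item run from 0 to 4 (an assumed range, used only for illustration) gives 5^5 = 3,125 combinations.

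- Reading A: the fallback applies in 0 of 3,125.
- Reading B: it applies in 56 of 3,125. By fever count, the combinations with N < F are 1 (F = 1), 5 (F = 2), 15 (F = 3) and 35 (F = 4), and 1 + 5 + 15 + 35 = 56.

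The zero under reading A holds for any range. The 56 is not an estimate of how often the fallback would be used in the trial, because the combinations are not equally likely.

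**Single participants.**

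| Reported episodes | Reading A | Reading B |
|---|---|---|
| 1 upper respiratory, 1 fever | 2 | max(1, 1) = 1 |
| 1 upper respiratory, 2 fever | 3 | max(1, 2) = 2 |
| 1 fever only | 1 | max(0, 1) = 1 |
| 1 upper and 1 lower respiratory, no fever | 2 | max(2, 0) = 2 |
| 1 upper, 1 lower, 1 gastrointestinal, 1 fever | 4 | max(3, 1) = 3 |

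**Excess of A over B.** (N + F) − max(N, F) = min(N, F). The readings agree for a participant with no fever, or with fever and no listed infection. They differ for everyone who reports both.

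**Effect on the comparison.** The between-arm difference under A minus that under B equals the mean of min(N, F) in the intervention arm minus the same mean in the placebo arm. The article gives nothing from which to evaluate either mean. If treatment affects neither infections nor fever, the two means are equal in expectation and the difference is unchanged.

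**The case against.** The strongest reply is that the fallback already settles the matter. It sets the sum against the fever count as two separate quantities. One reading makes that sentence impossible and the other makes it work, so an ordinary reader takes the one that works: four infections are summed, with fever as a floor. This stands as evidence of intention. It means that double counting of febrile infections is one reading of the text and not the plan's settled rule, although a reader might infer the latter from the list and the sum sentence. It does not remove the contradiction, because the text nowhere says that fever is left out and its literal wording puts fever in.

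A second reply is that item-level scoring belongs in the full protocol or analysis plan, which are not shown. That would answer a complaint of missing detail. Here the article does state a derivation rule, and its sentences conflict.

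A third reply concerns size. A reader might infer that the mean total, or the difference between the arms, is inflated by the share of infections that are febrile. The documents do not support this. They give no febrile share, and the relation holds only if every fever episode belongs to a listed infection. If the febrile share f were the same in both arms, both means would be multiplied by the same 1 + f, so a zero difference would stay zero and the ratio of the means would not change. This reply stands in full.

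The two fever thresholds also matter little: they differ only for a temperature of exactly 38.0 °C, and only one fever item is collected.

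**Conclusion.** The definition of total infection frequency is self-contradictory and should be corrected before analysis. Taken literally, fever is an addend, a febrile infection scores 2 and the fallback can never apply. The fallback works only with fever outside the sum, which is evidently what was meant.

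That the literal rule and the fallback exclude each other needs no assumption beyond non-negative counts. The readings differ by min(N, F) per participant. What this does to the arm means is unknown, and no bias towards either arm is shown.

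The reach is limited to this one secondary endpoint. The upper and lower respiratory infection endpoints are separate counts and are unaffected, as are the primary endpoint and the sample size. Severity: should be fixed, and no higher.

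**What to change.** Replace the sum and fallback sentences by one definition: total infection frequency = max(upper respiratory + lower respiratory + gastrointestinal + cystitis episodes, number of fever episodes). State expressly that fever is not an addend. Use one fever threshold throughout, the same as in the questionnaire item.

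The cost is one sentence in the endpoint definition, carried into the analysis program. The five items are already asked for separately, so the questionnaire and the sample size stay as they are. The change should be recorded before treatment allocation is linked to the infection data.

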**Fig. 1 Fig1:**
[figure not shown]
Overview of the study flow. Abbreviations: *EORTC QLQ-FA12* European Organization for Research and Treatment of Cancer – Cancer related Fatigue; *EORTC QLQ-C30* European Organization for Research and Treatment of Cancer – Core Quality of life questionnaire with 30 items; *FACIT-F* Functional Assessment of Chronic Illness Therapy-Fatigue; *FACIT-F FWB* Functional Assessment of Chronic Illness Therapy-Fatigue – Functional Well-being; *GDS-15* Geriatric Depression Scale with 15 items; *UICC* Union for International Cancer Control

In total, 456 eligible CRC patients are being randomized in order to analyze 410 for the primary endpoint after an expected drop-out rate of 10%. The trial schedule is presented in Table 3.

**Table 3 Tab3:** Detailed schedule of all observations to be performed during the clinical trial

Procedure	Screening Visit for eligibility	Visit 1 Start of treatment	Visit 2 End of rehabilitation	Collection of data via questionnaire/ phone and blood/urine sampling by GP
Rehabilitation clinic	Admission	–	Discharge	–
Time-point of data assessment	–	Day 1	Day 12–21	Week 13–16
Planned doses of vitamin D_3_ per day	–	Individualized initial dose (20,000 or 40,000 IU, followed by 2000 IU per day) for day 1–11	Maintenance dose of 2000 IU per day for day 12–21	–
Inclusion/exclusion criteria	●	●		
Written informed consent	●			
Randomization		●		
Trial medication intake		●	●	
Subject diary regarding days of drug administration		●	●	
Physical examination (weight, height, waist circumference)	●			
Urinary pregnancy test for women of childbearing potential	●			
Assessment of CRC treatment	●			●
Concomitant diseases / Medical history	●			
Concomitant medication	●			●
Query about concomitant use of vitamin D_3_ or vitamin D analogs in self-medication in addition to trial medication				●
Fatigue	●			●
Functional well-being, QoL, infection frequency, and depression	●			●
Blood sampling for biomarker efficacy and safety endpoints	●		●	●
Urine sampling for safety endpoints	●		●	●
(S)AE recording and protocol deviations		●	●	●

Abbreviations: *CRC* colorectal cancer; *GP* general practitioner; *QoL* Quality of life; *SAE* Serious adverse event

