### Statistical methods

All analyses will be done using SAS software version 9.4 or higher. Homogeneity of the treatment groups will be described by comparison of the demographic data and the baseline values of key variables. All statistical tests will have a two-sided significance level of 0.05. Besides, 95% confidence intervals will be estimated for all outcomes in the placebo and verum group.

The primary analysis will test the null hypothesis.

H_0_: The FACIT-F fatigue subscale at week 13–16 is the same in the two groups.

versus the alternative hypothesis.

H_1_: The FACIT-F fatigue subscale at week 13–16 is different in the two groups.

The primary endpoint FACIT-F fatigue subscale will be analyzed with an intention-to-treat approach. The intention-to-treat population will include all randomized study participants with data for the primary endpoint and who did not withdraw consent during the trial. A per-protocol analysis will be done additionally as a sensitivity analysis. The per-protocol population will exclude study participants who meet the following criteria:
Fatigue questionnaire missing at trial week 13–16Error in timing of collection of fatigue questionnaire at trial week 13–16After enrollment, it becomes evident that patient met exclusion criteria at time of recruitment or did not meet inclusion criteria.Incompliance to trial medication (defined as intake of less than 80% of capsules) unless treatment was terminated due to safety reasonsSelf-reported intake of vitamin D or vitamin D analogs in addition to the trial medication.Criteria for discontinuation of study medication were met but study medication intake was continued.

We will test on normal distribution for the outcome FACIT-F fatigue subscale with the Shapiro-Wilks test. If normal distribution can be assumed, the primary test statistic will be the two-sample t-test for the mean difference. If normal distribution cannot be assumed for the FACIT-F fatigue subscale, we will log-transform the FACIT-F fatigue subscale and test for normal distribution once more with the Shapiro-Wilks test. If normal distribution can neither be assumed for FACIT-F fatigue subscale nor log-transformed FACIT-F fatigue subscale, a Wilcoxon Rank-Sum test will be applied. In addition, appropriate 95% confidence intervals will be estimated for the FACIT-F fatigue subscale in the two groups and for the difference in FACIT-F fatigue subscale between the two groups.

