As a sensitivity analysis, a linear regression model will be carried out with FACIT-F fatigue subscale as the dependent variable and treatment group as the independent variable. The linear regression model will be adjusted for all variables named in the subgroup analysis while using some variables continuously instead of categorically (age, hemoglobin levels at screening, 25(OH)D levels at screening, BMI at screening, FACIT-F fatigue subscale at screening, insomnia scale at follow-up and pain scale at follow-up). If appropriate, missing covariate values will be imputed with multiple imputation.

All secondary endpoints with a continuous scale will be analyzed with the same statistical methods as described for the primary endpoint. All dichotomous secondary endpoints will be tested with a Chi^2^ test. AEs will be analyzed with descriptive statistics including frequencies of SAEs.

Lastly, the success of the personalized vitamin D_3_ intervention in raising the serum 25(OH)D level will be evaluated in the intervention group at trial day 12–21. Furthermore, the success of the maintenance dose to maintain sufficient vitamin D status in the intervention group will be evaluated in trial week 13–16. To be successful, the mean 25(OH)D levels in the group with personalized vitamin D_3_ intervention should be higher than 50 nmol/L. This translates into the following test hypotheses:
H_0_: Mean 25(OH)D_personalized intervention_ ≤ 50 nmol/LH_1_: Mean 25(OH)D_personalized intervention_ > 50 nmol/L

To test these hypotheses, we will conduct a one-sample t-test on the mean 25(OH)D levels at a one-sided significance level of 0.025. 25(OH)D levels may be log-transformed if this improves the approximation of a normal distribution (to be tested with a Shapiro-Wilks test).

*Exploratory sub-project: “Determinants of the achieved 25(OH)D levels by the personalized vitamin D*_*3*_*intervention”*

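### Infection episode counts are routed through a continuous-data test cascade, so with many zeros the p-value will not test the stated mean difference, and the screening count is used in no efficacy analysis

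*Protocol article*

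**What the plan says.** **Endpoint (Protocol article, Outcomes and endpoints).** Patients state how many episodes of several kinds of infection they had over 12 weeks. The total is the sum, or the number of fever episodes if that is larger, so every value is a non-negative whole number. The plan then states: "Endpoints will be the mean differences in infection frequencies (total, upper respiratory, and lower respiratory tract infections) between intervention and placebo group", at week 13–16 only.

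**Analysis rule (Statistical methods).** "All secondary endpoints with a continuous scale will be analyzed with the same statistical methods as described for the primary endpoint". Dichotomous secondary endpoints get a chi-squared test. No third class is named. The primary-endpoint methods are:
- a Shapiro-Wilk test, then a two-sample t-test if normality is accepted;
- otherwise a log-transform and a second Shapiro-Wilk test;
- if that also fails, a Wilcoxon rank-sum test;
- alongside the test, 95% confidence intervals for each group and for the difference.

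The level is common to all tests: "All statistical tests will have a two-sided significance level of 0.05".

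**Baseline (Table 3).** The row "Functional well-being, QoL, infection frequency, and depression" is marked at screening and again at week 13–16. The fatigue, quality-of-life, depression and functional well-being scores each have a change-from-baseline endpoint; infection does not. The screening infection count is also absent from the subgroup variables, from the covariates of the adjusted linear regression and from those of the exploratory sub-project.

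**The concern.** A count summarised by a mean difference can enter only the continuous-scale route, and that route suits small counts poorly. The logarithm of zero does not exist and no offset is given. A variable with a large spike at zero will not pass a normality test at this sample size. The cascade then ends in a rank test with heavy ties at zero, while the endpoint and the planned interval concern a difference in means. The p-value and the interval could point different ways, and the plan does not say which one carries the conclusion.

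The screening count is the natural covariate for the follow-up count. It is already collected, yet no efficacy analysis names it.

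Infection frequency is listed under Objectives, and the Abstract expects an effect on it. What is at stake is how three secondary endpoints are read.

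**Working it through.** **1. The plan's own figure.** The only sample size is for the primary endpoint: "With a significance level of 0.05 and 80% power, 205 patients are needed in each group". The target there is 3 points on the FACIT-F fatigue subscale, compared by t-test. The assumed mean and SD are those "which were 38.5 and 10.8, respectively"; allocation is 1:1 (Study design).
- Normal approximation: n = 2 × (1.960 + 0.842)² × 10.8² / 3² ≈ 203.4, so 204 per arm.
- Exact t calculation: 204.4, so 205 per arm; power at 205 is 80.3%.
- Drop-out: 410 / 0.9 = 455.6, so 456.

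The figure reproduces. No power is claimed for infections; 205 per arm is used below as the available size.

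**2. Assumptions.** The documents give no infection rate, overdispersion, effect or baseline correlation. The main runs assumed a placebo mean m of 0.3–1.2 episodes per 12 weeks, negative binomial dispersion k of 0.3–2 and a mean ratio of 0.65. Half or nine tenths of each patient's underlying rate was shared between the two time points, giving baseline/follow-up correlations of 0.06–0.60. The screening question is taken to have the same 12-week look-back. Runs used 600–2000 simulated trials per setting.

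**3. Share of zeros.** P(0) = (1 + k·m)^(−1/k).
- m = 0.3, k = 1: 1/1.3 = 77%
- m = 0.8, k = 1: 1/1.8 = 56%
- m = 1.2, k = 1: 1/2.2 = 45%

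Shapiro-Wilk rejected in 100% of simulated trials, on the raw counts and (in the 600-trial runs) on log(count + 1). So even with an offset supplied, the cascade ends in Wilcoxon.

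**4. Power (%), 205 per arm, mean ratio 0.65.** The count model is Poisson regression with robust variance; the last column adds log(screening count + 0.5).

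| Effect | m | k | Shared part | Wilcoxon | t-test | Count model | + screening count |
|---|---|---|---|---|---|---|---|
| Rate reduction | 0.3 | 1 | 0.5 | 43.2 | 48.0 | 48.4 | 49.0 |
| Rate reduction | 0.5 | 0.3 | 0.5 | 67.0 | 71.2 | 72.0 | 72.7 |
| Rate reduction | 0.8 | 1 | 0.5 | 68.2 | 76.8 | 77.5 | 80.0 |
| Rate reduction | 0.8 | 1 | 0.9 | 68.8 | 77.1 | 77.6 | 83.2 |
| Rate reduction | 1.2 | 2 | 0.9 | 50.5 | 68.2 | 69.7 | 89.0 |
| All-or-none | 0.8 | 1 | 0.5 | 88.6 | 71.2 | 69.7 | 71.5 |
| All-or-none | 0.8 | 1 | 0.9 | 88.6 | 69.4 | 68.7 | 73.5 |
| All-or-none | 1.2 | 2 | 0.9 | 89.7 | 61.3 | 60.4 | 77.3 |

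Over the 16 rate-reduction settings, Wilcoxon is 5–19 points below the unadjusted count model. The screening count adds about 0 points at correlations of 0.1 or less and up to 19 at 0.60. With no effect, all methods rejected in 5.0–6.5% of trials.

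**5. Other assumptions, ratio 0.70.**
- Means 0.5–1.5, rate reduction: Wilcoxon 39–67%, count model 48–79%.
- Means 0.5–1.5, all-or-none: Wilcoxon 60–93%, count model 45–70%.
- Means 0.1–0.2, as might apply to lower respiratory infection: Wilcoxon 17–26%, count model 17–27%.

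**6. The test does not track the endpoint.** At m = 0.8 both effect shapes give the same mean difference: 0.8 × 0.35 = 0.28 episodes. Zeros in the treated arm differ. Under a rate reduction they are 1/(1 + 0.52) = 65.8%, which is 10.2 points above the placebo 55.6%. Under all-or-none they are 0.35 + 0.65 × 0.556 = 71.1%, which is 15.6 points above. Wilcoxon power moves from 68% to 89% with the mean difference unchanged, so it responds to something other than the stated quantity.

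**The case against.** **No mean difference will be reported.** A reader might infer this from a rank test. The documents do not support it: Statistical methods plans an interval for the between-group difference, and the rule for continuous secondary endpoints carries that over. What remains is a mismatch between test and estimate.

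**The endpoints simply lose power.** This is tempting but not supported. The protocol states neither an infection rate nor an effect shape. Under an all-or-none effect the order reverses in favour of Wilcoxon, and for rare events there is little to choose.

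**The missing count model is not the cause.** This stands. The t-test, already in the plan, tests the stated mean difference and comes within about 2 points of the unadjusted count model in every rate-reduction setting. Any loss comes from the normality gate. What a count model adds is a rate ratio and a natural place for the screening count.

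**The screening count may predict little.** Also fair. Patients enter within 9 months of surgery, some after chemotherapy or radiotherapy, and the two look-back windows fall in different parts of the year. The count may also serve in the planned baseline comparison, so it is not wasted outright. Leaving out a change-from-baseline endpoint for a recalled count is defensible.

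**The article is condensed.** Counts are never called continuous, and an unseen analysis plan may treat them separately. The shared-methods rule could also be stretched to an adjusted regression on the outcome's own baseline, though the text does not say so. It would be wrong to infer that no count analysis exists anywhere. But the article does state a rule for secondary endpoints, and that rule leaves these counts only one place to go.

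**Conclusion.** The point holds in limited form. As stated, the plan sends three count endpoints down a route whose log step cannot be run at zero. If zeros are common, the route ends in a test that does not address the mean difference the plan names. The planned interval for that difference could then disagree with the p-value. The screening count enters no stated efficacy analysis.

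The consequence for power is conditional. With a proportional rate reduction (assumed ratio 0.65–0.70, mean of about 0.5 episodes or more), the unadjusted count model gains roughly 5–19 points over Wilcoxon. The screening count then adds between about 0 and nearly 20 points, depending on the baseline correlation. The gain reverses under an all-or-none effect and nearly vanishes at means of 0.1–0.2. All these figures rest on assumed rates. The case for change therefore rests mainly on matching test to endpoint, with power second.

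These are secondary endpoints; the primary analysis and the sample size are unaffected. Severity is minor to moderate.

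**What to change.** Add a sentence to Statistical methods that takes the infection counts out of the continuous-data rule:
- Analyse total, upper respiratory and lower respiratory counts each by negative binomial regression, or by Poisson regression with robust variance. Choose one in advance.
- Include treatment and the screening 12-week count of the same infection type as covariates.
- Report the rate ratio and the model-based mean difference, each with a 95% confidence interval, and take the p-value from the same model.
- Keep Wilcoxon as a sensitivity analysis, which also covers an all-or-none effect.

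The cost is one sentence and standard SAS code on data already collected. The plan's provision for multiple imputation of covariates can be extended to missing screening counts. The drawback is less power than Wilcoxon if treatment abolishes infections in some patients and leaves the rest unchanged. If a count model is not wanted, applying the t-test to these endpoints without the normality gate would at least align test and estimate, but would leave the screening count unused.
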